## Abstract

**Background:** Emerging adults who do not successfully transition from compulsory education to the upper secondary level have a greater risk of developing mental illness than their working peers. Early intervention is important in these cases; the course of an illness can be positively influenced if treated early and without delay, and consequently, the illness will not affect the professional and personal development of the emerging adults any further. Postponing treatment of a mental illness increases the risk of chronification of the disease. Up to now, vocational integration programs have been mostly educationally oriented. To recognize and treat mental illness in a timely way, we developed an intervention that includes psychotherapy support in a vocational integration program for emerging adults who have not successfully transitioned from compulsory education to the upper secondary level.

**Aim:** The aim of this study is to investigate the effectiveness of the described intervention, which will be delivered to all emerging adults aged 16–29 entering the vocational integration program. Another objective is to determine if it is worthwhile and feasible to proceed with testing the intervention in a full-scale clinical trial. Conducting research with this population can be very difficult, which makes it especially important to test the feasibility of a clinical trial.

**Methods:** A single group clinical trial will be conducted to examine the effectiveness of the intervention described above. Emerging adults aged 16–29 entering a vocational integration program will be recruited. Participants will provide informed consent and complete pre-intervention measures; they then take part in the intervention group in addition to the regular vocational integration program. The primary outcomes for this study are an increase in work ability, mental health literacy, and mental health. Demographic information, vocational biography, and satisfaction with the intervention will also be collected. Questionnaire data will be collected at pre-intervention, post-intervention, and 6-month follow-up.

**Ethics and dissemination:** The study was approved by the Ethics Committee of the Canton of Zurich (2017-00936) and registered in https://clinicaltrials.gov (NCT03328286) before recruitment started. The results will be reported in future scientific publications and international conference presentations.

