In vocational integration programs, emerging adults work on skills needed for entering the labor market. In the program in which we are conducting our study, participants learn how to write an application dossier and how to conduct a job interview, but they also work on educational deficits, such as in general knowledge and mathematics. In addition, they have regular external work assignments so that they get to know the job for which they are applying. To strengthen the emerging adults in vocational integration programs, the intervention in this study targets other aspects, such as work ability, mental health literacy, and mental health. We assume that the psychotherapeutic services that we plan to provide will lead to improvement in the participants’ work ability, mental health literacy, and mental health and therefore, together with the support of the vocational integration program, will facilitate the emerging adults’ integration in the labor market.

Work ability is defined as the ability to master certain tasks in very specific situations (Prümper and Richenhagen, 2011), the skill to master tasks in a certain moment in time (Ilmarinen et al., 2005). Historically, the term work ability is strongly connected with the Work Ability Index (Tuomi et al., 1994), and it is often operationalized using that measure.

To assess the participants’ work ability more thoroughly, we will also measure their self-esteem and self-efficacy. Self-esteem and self-confidence have a central place in psychology in general and in relation to almost all disorders in particular (Potreck-Rose and Jacob, 2015). Self-esteem is seen as a psychosocial resource. A lack of this resource is often related to various mental disorders, such as depression (Turner et al., 2004) or eating disorders (Brockmeyer et al., 2013).

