In this study, we measure mental health literacy through young people’s help-seeking behavior and their current mental health literacy by asking different questions on their knowledge about mental health. We also include stress in the mental health literacy definition, since stress and mental disorders caused by stress are very common among emerging adults (Bayram and Bilgel, 2008). Perceived stress is often related to a low quality of life (Marshall et al., 2008).

Finally, we measure mental health through a self-report inventory that rates physical and psychological symptoms and a self-rating questionnaire that assesses impairment due to depressive symptoms.

This paper describes the study protocol for a novel intervention that we developed with the aim to complement the educationally oriented support provided in vocational integration programs with a psychotherapeutic service. We also focus on the feasibility of a clinical trial with emerging adults in vocational integration programs. The model that we developed simplifies early recognition and treatment of mental distress in emerging adults. By integrating a psychotherapist in the vocational integration program, we facilitate the emerging adults’ access to health care professionals. In the intervention that we designed, a psychotherapist holds a weekly group meeting with the participants, so that they become familiar with the psychotherapist and have the opportunity to build a trustful relationship. The goal of the group meetings is to provide and discuss psychoeducational information, to foster active confrontation with one’s own mental health problems, and to teach stress reduction techniques, such as mindfulness-based stress reduction (MBSR) (Kabat-Zinn, 2009).

To measure the outcome of the intervention, we chose the following indicators: work ability, mental health literacy, and mental health.

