### Objectives

#### Primary Research Question and Hypotheses

The main objective of this study is to investigate if the intervention—the integration of a psychotherapist in a vocational integration program—facilitates access to the labor market for mentally burdened emerging adults by increasing their work ability and mental health literacy and by improving their mental health.

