##### Main Hypothesis

Work ability increases significantly from *t*_0_ to *t*_2_.

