##### Secondary Hypotheses

Mental health literacy increases significantly from *t*_0_ to *t*_2_. Mental health increases from *t*_0_ to *t*_2_.

Another objective of this study is to determine the feasibility of the intervention and whether it is possible to conduct a clinical trial with unemployed emerging adults who are facing numerous challenges in their transition to adulthood. This study aims to identify implementation difficulties and establish procedures for a potential large-scale trial, including the recruitment of a control group receiving treatment as usual.

The aims are to evaluate the feasibility of the recruitment process and study uptake. Furthermore, we analyze the acceptability and credibility of the therapeutic concept in a non-clinical setting among professionals in vocational training and the emerging adults in these programs.

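### The abstract names three primary outcomes, the hypotheses rank one as main and two as secondary, and no scale is named to decide the main hypothesis

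*Protocol article*

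**What the plan says.** The protocol article gives the outcome hierarchy in three places.

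- **Abstract, Methods:** "The primary outcomes for this study are an increase in work ability, mental health literacy, and mental health". All three constructs carry the primary label, unranked.
- **Primary Research Question and Hypotheses:** the main objective is easier access to the labor market "by increasing their work ability and mental health literacy and by improving their mental health". Again all three appear together.
- **Main Hypothesis and Secondary Hypotheses:** the main hypothesis is "Work ability increases significantly from" t0 to t2. Under the secondary heading stand "Mental health literacy increases significantly from" t0 to t2 and "Mental health increases from" t0 to t2.

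Table 1 lists WAI, SWE and RSES under work ability, each measured at all three visits. The Introduction explains the last two: "To assess the participants’ work ability more thoroughly, we will also measure their self-esteem and self-efficacy". It also says that work ability is often operationalized with the WAI, but does not designate the WAI as the measure that decides the hypothesis.

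The Analysis section refers to main outcome measures in the plural without listing them, sets a 5% level, and says that alpha will be adjusted, giving neither method nor family. Power and Sample Size Calculation uses alpha 0.05 and 95% power and names no outcome.

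**The concern.** A condensed article may leave detail to a fuller plan. Here it gives two hierarchies that cannot both hold. Under the Abstract, literacy and mental health are primary; under the Objectives they are secondary.

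Suppose literacy improves and work ability does not. The Abstract would let the authors report a positive primary outcome, while the Objectives would oblige them to report that the main hypothesis failed. The choice could be made after the data are seen.

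The same gap recurs one level down. Work ability has three scales and no stated rule for which one counts or how they combine, so the main hypothesis has no single defined test even if the Objectives are followed. This matters more in a single-group study, where a fixed hierarchy is one of the few protections against selective claims.

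**Working it through.** **1. The texts side by side**

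| Construct | Abstract | Hypotheses | Scales repeated at t0, t1, t2 (Table 1) |
|---|---|---|---|
| Work ability | primary | main | WAI, SWE, RSES |
| Mental health literacy | primary | secondary | PSQ, MHLS, GHSQ |
| Mental health | primary | secondary | ADS, BSI |

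The M-CIDI is given at t0 only and is used descriptively, so it is not a candidate test.

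**2. What each text implies for alpha**

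- Hypotheses, if one work ability measure decides: one primary test, alpha = 0.05.
- Abstract: three primary constructs. If success on any one counts, Bonferroni gives 0.05 / 3 = 0.0167 each.

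Bonferroni is used here for illustration, because the article names no method.

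**3. Reproducing the stated sample size**

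From the article: repeated-measures ANOVA F-test, within factors; f = 0.25; alpha = 0.05; power 0.95; three assessments (m = 3). Assumed because not stated: one group, correlation rho = 0.5 between visits, sphericity (epsilon = 1).

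Formulas: lambda = f² × N × m / (1 − rho); df1 = m − 1; df2 = (N − 1)(m − 1). Power is the probability that a noncentral F with these values exceeds the critical F.

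At N = 43:
- lambda = 0.0625 × 43 × 3 / 0.5 = 16.125
- df1 = 2, df2 = 42 × 2 = 84
- critical F at 0.05 = 3.105
- power = 0.951; at N = 42 it is 0.947

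So 43 is the smallest N that reaches 0.95, and the article's figure is reproduced.

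**4. The same calculation at alpha 0.0167**

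lambda and the degrees of freedom are unchanged. The critical F rises to 4.301 and power at N = 43 falls to 0.886 for each test. Reaching 0.95 per test takes N = 53 completers, which is 53 / 0.8 = 66.25, so 67 recruited when 20% are lost.

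**5. If all three must succeed**

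Under that rule no alpha split is needed. If each test has 95% power, the chance that all three succeed is about 0.86 with independent tests and about 0.90 with tests correlated at 0.7 (simulated).

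**6. Sensitivity to the assumed correlation between visits (N = 43)**

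| rho | Power at 0.05 | Power at 0.0167 | N needed at 0.05 |
|---|---|---|---|
| 0.3 | 0.856 | 0.731 | 60 |
| 0.5 | 0.951 | 0.886 | 43 |
| 0.7 | 0.997 | 0.990 | 27 |

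Of these three values, only rho = 0.5 returns the article's N.

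**The case against.** The strongest reply is that the body already ranks the outcomes. The main objective names all three constructs, the hypotheses beneath it put them in order, and the Abstract merely compresses the objective. On this view the fault is one loose label. That is a fair account of how the conflict may have arisen, and it is why the Abstract is the text to correct. It does not remove the conflict, because the Abstract uses the term primary outcomes without qualification and the Analysis section does not say which hierarchy it follows.

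A second reply is that the choice of scale and the details of the adjustment belong in an analysis plan that is not shown, and that the Introduction points to the WAI. The pointer is real and supports the fix below. The missing adjustment method would indeed be no finding by itself. It matters here only because the family to be adjusted differs between two printed statements.

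Third, this is a single-group study that admits it cannot control for confounders and bases the decision on a full trial on descriptive feasibility data. That limits what the hypothesis test can carry. But the article also sets out to examine effectiveness and states significance hypotheses, so the hierarchy still governs what can be claimed.

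Three stronger readings are tempting and are not supported:

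- **An inflated false-positive rate.** A reader might infer 1 − 0.95³ = 14.3% for three tests or 1 − 0.95⁸ = 33.7% for all eight repeated scales. Those figures need independent, unadjusted tests and a rule that any one success counts. The article announces an adjustment and states no such rule.
- **An alpha of 0.05 / 8 = 0.00625.** No text defines a primary family of eight tests.
- **The PSQ is misfiled under literacy.** The Introduction declares the choice ("We also include stress in the mental health literacy definition") and Table 1 follows it. One may prefer another grouping, but this is not an error in the plan.

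**Conclusion.** The point holds. The article states two incompatible outcome hierarchies, and its main hypothesis is attached to a construct with three scales and no named deciding one. The same results could therefore be reported as a primary success or as a failed main hypothesis.

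The sample size agrees with the single-primary reading: alpha is unsplit, and N = 43 gives power 0.951 for one test. Under the Abstract's reading with a Bonferroni split, each test has power 0.886, below the study's own 95% target. These figures rest on the assumed correlation of 0.5, on sphericity, and on the omnibus F-test over three visits that the article used; they do not give the power of the t0 to t2 contrast in a mixed model. The 0.886 is power per construct; the chance that at least one of three succeeds would be higher.

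The contradiction itself rests on no numerical assumption. Which hierarchy the registry entry or the full protocol carries cannot be judged from this article.

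**What to change.** 1. Correct the Abstract so that it matches the Main and Secondary Hypotheses.
2. Name change in WAI total from t0 to t2 as the single primary outcome, tested at 5% with no split. The Introduction already presents the WAI as the usual way to operationalize work ability.
3. List SWE, RSES and the literacy and mental health scales as secondary, and apply the announced alpha adjustment to that family, for example by Holm's method.
4. If three co-primary outcomes are really intended, say so in both places, name the measure for each, state whether any or all must succeed, and restate power and sample size for that rule.

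Cost: the first three steps change wording and leave the alpha behind N = 43 as it is. The sponsor gives up claiming primary success on literacy, symptoms, self-esteem or self-efficacy. The ethics committee and the registry must be notified, as the article's Declarations already provide for protocol changes. The fourth route costs more: on the assumptions above, a Bonferroni split needs 53 completers, or 67 recruited, to keep 95% power per test.

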## Introduction

In Switzerland, after 9 years of compulsory education, 53% of young adults start an apprenticeship, 31% enroll in an upper secondary school, and 16% do not have an interim solution (Keller, 2014). This means that in Switzerland, every sixth young adult does not transition directly from compulsory education to upper secondary education/training. For young people who, after completing lower secondary education, cannot immediately commence vocational education and training (VET) or enroll in a school offering general upper secondary education, various transitional options for vocational integration are available.

Vocational integration programs are voluntary interim solutions for young people who for various reasons do not find an apprenticeship or secondary school after completing compulsory schooling. The programs have been designed to facilitate the transition to vocational or school-based training (Annen et al., 2010). The training period is usually limited to 1 year. The focus of the various programs can vary: there are more compensatory, remedial programs that focus on school, language, or other deficits. Some young people use the year in the bridge year course as a decision-making aid when choosing a career. For others, it is a buffer to bridge the waiting period until the start of their apprenticeship or secondary school. Overall, the programs all have the same aim: vocational integration (Meyer, 2004).

A look at the mental health of the participants of these programs reveals a significantly higher percentage of mental distress among the emerging adults than among their peers in apprenticeships or at upper secondary schools (Sabatella and von Wyl, 2014): the study found that 74% of the participants showed signs of mental distress. The causes of this higher percentage are twofold: for one, not finding training/workplace is a burden. For another, emerging adults who already have mental distress may struggle with finding an apprenticeship (Schaufeli, 1997).

Regardless of the cause, the consequences are the same: for unemployed emerging adults with severe mental health problems, it is difficult to find an apprenticeship (OECD, 2014). Many of these emerging adults have a mental disorder that has not been diagnosed or treated. This fact is reflected in the increasing number of emerging adults receiving a disability pension due to mental health problems. Although the total number of disability pensions has decreased since 2005 due to several reforms, there is no decrease among the youngest age group. Since 1995, newly awarded pensions due to mental disorders among the youngest disability pension recipients (aged 18–19) have registered a yearly increase of 6%; among 20- to 24-year-olds, the yearly increase is 2% (OECD, 2014). This is made worse by the fact that emerging adults often do not seek professional help when they experience mental health problems. The reasons for this can be manifold: negative beliefs and attitude toward professional help-seeking, fear of the stigma of mental health problems, a lack of emotional competence, or help-negation when help is needed the most (Rickwood et al., 2005). Baer et al. (2016) analyzed 400 dossiers of emerging adults who had been awarded a disability pension between 2010 and 2013 due to mental health problems and found that the pensions had been awarded before their 23rd birthday, and only 14% had completed an apprenticeship. The researchers suggested different measures: prioritization of completing an apprenticeship, systematic interdisciplinary assessment, and early recognition and intervention of mental disorders in schools and vocational training.

In vocational integration programs, emerging adults work on skills needed for entering the labor market. In the program in which we are conducting our study, participants learn how to write an application dossier and how to conduct a job interview, but they also work on educational deficits, such as in general knowledge and mathematics. In addition, they have regular external work assignments so that they get to know the job for which they are applying. To strengthen the emerging adults in vocational integration programs, the intervention in this study targets other aspects, such as work ability, mental health literacy, and mental health. We assume that the psychotherapeutic services that we plan to provide will lead to improvement in the participants’ work ability, mental health literacy, and mental health and therefore, together with the support of the vocational integration program, will facilitate the emerging adults’ integration in the labor market.

Work ability is defined as the ability to master certain tasks in very specific situations (Prümper and Richenhagen, 2011), the skill to master tasks in a certain moment in time (Ilmarinen et al., 2005). Historically, the term work ability is strongly connected with the Work Ability Index (Tuomi et al., 1994), and it is often operationalized using that measure.

To assess the participants’ work ability more thoroughly, we will also measure their self-esteem and self-efficacy. Self-esteem and self-confidence have a central place in psychology in general and in relation to almost all disorders in particular (Potreck-Rose and Jacob, 2015). Self-esteem is seen as a psychosocial resource. A lack of this resource is often related to various mental disorders, such as depression (Turner et al., 2004) or eating disorders (Brockmeyer et al., 2013).

Self-efficacy is similarly relevant. In view of the fact that self-esteem and experiencing self-efficacy are essential dimensions of the ability to work and that self-efficacy plays a significant role, especially for (re-)entrants into everyday working life (e.g., after a period of illness) (Black et al., 2018), it is worth taking a closer look at these dimensions. “Self-efficacy,” coined by Bandura in 1977, plays a major role in Bandura’s social cognitive theory (Bandura, 2001). Bandura found that heightened perceived self-efficacy before the start of psychotherapy and an increase in perceived self-efficacy during the therapeutic intervention were important predictors of the success of the treatment. A newer study has confirmed that for emerging adults with a diagnosed mental disorder, work is a resource. It gives them the possibility of becoming financially independent, and they experience an increase in their self-esteem and self-efficacy (Torres Stone et al., 2016). Early sensitization or early intervention services for mental disorders are generally recommended (Chan et al., 2015); however, such psychotherapeutic services focus less on self-esteem and self-efficacy and more on health competencies (knowledge in the field of mental health, help-seeking behavior, etc.).

Another important indicator is mental health literacy. Mental health literacy is the ability to obtain, read, understand, and use health care information to make appropriate decisions, seek help, and follow treatment instructions (Jorm et al., 1997). In the field of health literacy, the connection between mental health literacy and help-seeking behaviors is widely confirmed (Wei et al., 2015). It is therefore also recommended that these be anchored in school education in order to reduce barriers to seeking help and counteract the help-negation effect (not utilizing needed help) (Rickwood et al., 2005). However, further studies are needed to examine the course of people’s help-seeking behaviors over time or against the background of changing conditions (Wei et al., 2015).

In this study, we measure mental health literacy through young people’s help-seeking behavior and their current mental health literacy by asking different questions on their knowledge about mental health. We also include stress in the mental health literacy definition, since stress and mental disorders caused by stress are very common among emerging adults (Bayram and Bilgel, 2008). Perceived stress is often related to a low quality of life (Marshall et al., 2008).

Finally, we measure mental health through a self-report inventory that rates physical and psychological symptoms and a self-rating questionnaire that assesses impairment due to depressive symptoms.

This paper describes the study protocol for a novel intervention that we developed with the aim to complement the educationally oriented support provided in vocational integration programs with a psychotherapeutic service. We also focus on the feasibility of a clinical trial with emerging adults in vocational integration programs. The model that we developed simplifies early recognition and treatment of mental distress in emerging adults. By integrating a psychotherapist in the vocational integration program, we facilitate the emerging adults’ access to health care professionals. In the intervention that we designed, a psychotherapist holds a weekly group meeting with the participants, so that they become familiar with the psychotherapist and have the opportunity to build a trustful relationship. The goal of the group meetings is to provide and discuss psychoeducational information, to foster active confrontation with one’s own mental health problems, and to teach stress reduction techniques, such as mindfulness-based stress reduction (MBSR) (Kabat-Zinn, 2009).

To measure the outcome of the intervention, we chose the following indicators: work ability, mental health literacy, and mental health.

